### Sample size determination, randomization, and statistical analysis

Individual randomization of physicians within a group-practice and individual patients to either the control or intervention arm of the study is not feasible [32]. A cluster randomized design was chosen in which family physicians within a group practice were randomized to the same experimental group (control or intervention) and considered a cluster. Randomization of clusters will be conducted by a biostatistician using a computer-generated list and all of a physician’s patients will receive the same experimental treatment (control or intervention). Our protocol defines a multi-level analysis facilitating analysis of the intraclass correlation coefficient (ICC) for each primary group-level outcome (patients, FP, clinics/clusters) [32]. To ensure an even distribution of cluster-level characteristics between experimental groups, clusters will be randomized within strata based on membership in the Physician Integrated Network (PIN) and/or Uniting Primary Care Oncology Network (UPCON) [28]. These represent two quality improvement initiatives in Manitoba (Table 2). Clusters will be block randomized based on the number of collaborating FPs within a practice. An absolute increase in FOBT screening rates of 15% from the current 42% in Manitoba will be considered clinically significant [14]. Sample size was determined by a biostatistician using PASS (Power and Sample Size, 2002) software and a computer simulated ICC value of 0.6 [33] taking into consideration the clustered design of the trial [34]. This is a very conservative estimate of the minimum detectable effect size (MDEF) given the proposed sample size. Based on logistic regression a cluster size of 41 clusters each enrolling 30 to 35 patients (of which 80% are in the group that does not utilize the supplied intervention/magnet and 20% are in the group that does utilize the intervention/magnet; 1230 observations) will achieve 90% power at a 0.05 significance level to detect a change from the baseline value of 0.400 to 0.550 and corresponds to an odds ratio of 1.833. In the event that family physician collaboration/retention and/or patient recruitment proves to be more difficult than anticipated, a logistic regression with a cluster size of 28 (840 observations) achieves 80% power with the same outcomes.

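### The stated ICC of 0.6 gives about 17–23% power with 41 clusters and 13–17% with 28, not 90% and 80%, so the ICC and the powers cannot both be right

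*Protocol article*

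**What the plan says.** All the inputs stand in the protocol article under *Sample size determination, randomization, and statistical analysis*.

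- **Clustering:** the calculation used "a computer simulated ICC value of 0.6 [33] taking into consideration the clustered design of the trial". The text adds: "This is a very conservative estimate of the minimum detectable effect size (MDEF) given the proposed sample size".
- **Main scenario:** "a cluster size of 41 clusters each enrolling 30 to 35 patients", given as "1230 observations", which "will achieve 90% power at a 0.05 significance level to detect a change from the baseline value of 0.400 to 0.550". This "corresponds to an odds ratio of 1.833".
- **Split of the binary covariate:** "80% are in the group that does not utilize the supplied intervention/magnet and 20% are in the group that does utilize the intervention/magnet".
- **Fallback if recruitment is poor:** "a logistic regression with a cluster size of 28 (840 observations) achieves 80% power with the same outcomes".

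The same section randomises whole group practices, so treatment does not vary within a cluster, and sets an intention-to-treat analysis. The abstract describes 36 clusters, with 76 physicians enrolling 30 patients each.

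**The concern.** An ICC of 0.6 for a binary outcome means that most of the variation lies between clusters. Patients added within a cluster then contribute almost nothing, and power depends on the number of clusters. A total of 41 or 28 clusters is small for a 15-point difference under such clustering, yet the text claims 90% and 80% power.

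Two things rest on these figures. The first is the claim, repeated under *Benefits*, that the study was powered for a 15-point increase. The second is the fallback, which tells the team that 28 clusters are enough. If the ICC is as printed, a null result would say little about the intervention. If it is not, the printed ICC misdescribes the design.

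**Working it through.** **Inputs from the document.** ICC 0.6; m = 30 patients per cluster (41 × 30 = 1230; 28 × 30 = 840); p0 = 0.40, p1 = 0.55; α = 0.05; split 80/20.

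**Assumptions.** The test is two-sided (sidedness is not stated). A 1:1 split is shown beside the printed 80/20, because the randomised comparison is between arms. The ICC is taken on the proportion scale.

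**What reproduces.** The odds ratio: (0.55/0.45) / (0.40/0.60) = 1.833, as stated.

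**Step 1: design effect.** DE = 1 + (m − 1) × ICC = 1 + 29 × 0.6 = 18.4.

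**Step 2: effective sample size.** 1230/18.4 = 66.8; 840/18.4 = 45.7.

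**Step 3: power.** With N the effective size and B the fraction in the smaller group, p̄ = B·p1 + (1 − B)·p0 and

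power = Φ[(0.15 − 1.96·SE₀)/SE₁], where SE₀ = √{p̄(1 − p̄)/(N·B(1 − B))} and SE₁ = √{p1(1 − p1)/(N·B) + p0(1 − p0)/(N(1 − B))}.

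Example, 41 clusters at 80/20: p̄ = 0.43, SE₀ = 0.1514, SE₁ = 0.1517, so power = Φ[(0.15 − 0.2968)/0.1517] = Φ(−0.97) = 16.7%.

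| Scenario | Stated | ICC 0.6, 1:1 | ICC 0.6, 80/20 | No clustering, 1:1 | No clustering, 80/20 |
|---|---|---|---|---|---|
| 41 × 30 | 90% | 23.0% | 16.7% | >99.9% | 98.9% |
| 28 × 30 | 80% | 17.0% | 12.7% | 99.2% | 93.9% |

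The stated powers match neither the printed ICC nor an unclustered calculation.

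**Step 4: can larger clusters help?** With 35 per cluster the results for 41 clusters are still 23.0% and 16.7%. As m grows, the effective size cannot exceed clusters/ICC = 41/0.6 = 68, which caps power at about 23%.

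**Step 5: clusters needed at ICC 0.6.** The unclustered requirement for 90% power is about 462 (1:1) or 716 (80/20). Multiplying by 18.4 and dividing by 30 gives about 283 or 439 clusters. For 80% power the requirement is about 346 or 535, which gives about 212 or 328 clusters.

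**Step 6: the ICC that the stated powers imply.** At 80/20, 1230/716.4 = 1.717, so ICC = 0.717/29 = 0.025; and 840/535.0 = 1.570, so ICC = 0.570/29 = 0.020. At 1:1 the same steps give 0.057 and 0.049. These are roughly 10 to 30 times smaller than 0.6.

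**Step 7: other routes at ICC 0.6.**

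| Method | 41 clusters | 28 clusters |
|---|---|---|
| One-sided test | 26–34% | 21–26% |
| Cluster-level t-test | 16–23% | 12–17% |
| Beta-binomial simulation | 17–23% | 14–17% |
| ICC on the latent logit scale, simulation | 10–29% | 8–21% |

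**Step 8: if 0.6 is a slip for 0.06 (assumption).** DE = 1 + 29 × 0.06 = 2.74. For 41 clusters, power is 89.2% (1:1) or 72.8% (80/20). For 28 clusters it is 75.1% or 56.4%. The first figure at 1:1 fits the text; the 80% for 28 clusters does not.

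**The case against.** The mismatch itself has no good answer, but several points on the other side deserve weight.

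- **Rounding.** The stated powers are round numbers and the clusters are whole. A single ICC of 0.02 at 80/20 gives 92.2% and 79.8%; 0.05 at 1:1 gives 92.2% and 79.7%. So the slightly different ICCs in Step 6 are weak evidence of a second inconsistency. The fallback fails at 0.6 and at 0.06, but could be right if one of these smaller values was used. This stands.
- **A mislabelled input.** If 0.6 is entered as the R-squared with other covariates in the logistic-regression formula for a binary covariate, at a 1:1 split, power is 91.7% and 78.9%, close to both stated figures. This may be their origin, but that is conjecture. It does not rescue the text: an R-squared is not an ICC, that formula applies no cluster design effect, and with the printed 80/20 split it gives 76.6% and 60.3%.
- **The design described in the abstract.** With 76 × 30 = 2280 patients in 36 clusters (about 63 each), power at ICC 0.06 would be about 91% (1:1) or 76% (80/20), so the trial may be adequate if 0.6 is a misprint. At 0.6 it is still only about 21% or 15%. If a cluster in this calculation means a physician, since 30 to 35 is also the quota per physician, 76 clusters of 30 at 0.6 reach about 39% (1:1).
- **Users against non-users within clusters.** Read this way, an ICC of 0.6 gives over 99% power. That again is not 90% or 80%, and it is not the randomised intention-to-treat comparison.
- **Conservatism.** An ICC of 0.6 would indeed be a cautious input. What fails is that the sample size does not reflect it.

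**Conclusion.** The concern holds. At the printed ICC, two-sided power for 0.40 versus 0.55 is about 17–23% with 41 clusters and 13–17% with 28, against the stated 90% and 80%. The ranges span the 80/20 and 1:1 splits and rest on the standard design effect with a proportion-scale ICC. A one-sided test, a latent-scale ICC or larger clusters move the figures but leave them far below those stated.

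Which number is wrong cannot be settled from the document. Depending on the answer, the 36-cluster design in the abstract is either badly underpowered or close to adequate. The calculation as printed cannot be called very conservative. It must be corrected before the power statement or the 28-cluster fallback is relied on.

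**What to change.** 1. State what was entered as 0.6, the ICC actually used, its scale (proportion or latent logit), and whether a cluster is a practice or a physician.
2. Recompute power for the randomised comparison with a cluster-randomised formula, stating the split and sidedness, over a range of ICCs such as 0.02, 0.05 and 0.10. Include the 36 clusters given in the abstract.
3. If 0.6 stands on the proportion scale, delete the 90% and 80% figures and the claim of conservatism, and state power of about 20% for 41 clusters. If another ICC was used, correct the value.
4. Withdraw the 28-cluster fallback unless 80% reproduces under the corrected inputs, and align the statement under *Benefits* with the result.

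The cost is a recalculation, revised wording and possibly a less favourable stated power. No extra patients are needed for the correction.

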**Methods/design:**

A pragmatic, two-arm, randomized cluster controlled trial conducted in 22 community-based family practice clinics (36 clusters) with 76 fee-for-service family physicians in Winnipeg, Manitoba, Canada. Each physician will enroll 30 patients attending their periodic health examination and at average risk for colorectal cancer. All physicians will follow their standard clinical practice for screening. Intervention group physicians will provide a fridge magnet to each patient that contains information facilitating access to the study-specific colorectal cancer screening decision aids (telephone help-line and website). The primary endpoint is patient fecal occult blood test completion rate after four months (intention to treat model). Multi-level analysis will include clinic, physician and patient level variables. Patient Personal Health Identification Numbers will be collected from those providing consent to facilitate analysis of repeat screening behavior. Secondary outcome data will be obtained through the Clinic Characterization Form, Patient Tracking Form, In-Clinic Patient Survey, Post-Study Follow-Up Patient Survey, and Family Physician Survey. Study protocol approved by The University of Manitoba Health Research Ethics Board.

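### The power statement puts 30 to 35 patients in each cluster, but the protocol gives that quota to each physician, so the stated 90% and 80% do not describe the 36-cluster, 76-physician trial

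*Protocol article*

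**What the plan says.** The section on sample size, randomisation and statistical analysis defines a cluster as the participating physicians of one group practice, all allocated to the same arm. It then sizes the trial on "a cluster size of 41 clusters each enrolling 30 to 35 patients", and says that "1230 observations) will achieve 90% power at a 0.05 significance level". The target effect is a rise in completion from 0.40 to 0.55, given as an odds ratio of 1.833. If recruitment falls short, "a logistic regression with a cluster size of 28 (840 observations) achieves 80% power with the same outcomes". The calculation cites "a computer simulated ICC value of 0.6" and divides the patients 80/20 by whether they use the magnet.

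The enrolment text uses a different unit. The abstract reports "22 community-based family practice clinics (36 clusters) with 76 fee-for-service family physicians" and says: "Each physician will enroll 30 patients attending their periodic health examination and at average risk for colorectal cancer". The section on setting and participants and the legend to Figure 2 give 30 to 35 patients per family physician. Table 6 supplies 30 to 35 tracking forms to each physician. Table 5 expects 1,500 to 2,400 tracking forms from 50 to 80 physicians, which is 30 per physician.

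Clusters are blocked on their number of physicians, and the analysis model has three levels: patients within physicians, physicians within clusters, and clusters.

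**The concern.** The same 30 to 35 serves as the cluster total in the power calculation and as the physician quota everywhere else. With more than two physicians per cluster on average, the two cannot both hold. In a cluster trial, power depends on the number of clusters, the patients per cluster, the spread of cluster sizes and the ICC. The calculation has the first two wrong for this trial and is silent on the third.

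The power claim is also used. The Benefits section tells readers that the study is powered for a 15-point absolute increase, and the Discussion considers what a negative result would mean. How far a null result rules out a 15-point gain depends on the power of the design actually run.

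**Working it through.** **1. Inputs from the article.** 41 clusters with 1230 observations for 90%; 28 with 840 for 80%; 0.40 against 0.55; significance level 0.05 (taken as two-sided); ICC 0.6; an 80/20 split by magnet use; 36 clusters; 76 physicians; 30 patients per physician (30 to 35 in the methods).

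**2. Reproducing the stated figures.**
- 41 × 30 = 1230 and 28 × 30 = 840. Both totals need 30 patients per cluster.
- Odds ratio: (0.55/0.45)/(0.40/0.60) = 1.833. It reproduces.
- Power does not reproduce. With ICC 0.6 the design effect for 30 per cluster is 1 + 29 × 0.6 = 18.4. Then 1230/18.4 = 66.8 and 840/18.4 = 45.7 effective patients, for power of 23% and 17% (1:1), or 17% and 13% (80/20).
- With clustering ignored and the 80/20 split kept, power is 98.9% and 93.9%. A logistic-regression formula for a binary covariate, with the sample reduced by (1 − R²), gives 76.6% and 60.3% at R² = 0.6, and 92.5% and 80.2% at R² = 0.36. No variant tried returned both 90% and 80%.
- Solving back with 1:1 arms, 41 × 30 reaches 90% at ICC 0.057 and 28 × 30 reaches 80% at ICC 0.049.

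**3. The structure the article describes.** 76 × 30 = 2,280 patients; 2,280/36 = 63.3 per cluster (at 35 per physician, 2,660 and 73.9). Since 76/36 = 2.11 is not a whole number, sizes must differ. The most even split, 32 clusters of two physicians and four of three (64 + 12 = 76), has CV 0.15. The article does not give the actual distribution.

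**4. Power under both structures.** Design effect DE = 1 + ((1 + CV²)m − 1) × ICC, with m the mean cluster size; effective N = total/DE; power by the normal approximation for two proportions, 0.40 against 0.55, 1:1, two-sided 0.05. The CVs and the ICCs 0.05 and 0.10 are assumptions; 0.6 is the article's value.

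| Structure | CV | ICC 0.05: DE, effective N, power | ICC 0.10: power | ICC 0.6: power |
|---|---|---|---|---|
| 41 × 30 | 0 | 2.45, 502, 92% | 76% | 23% |
| 28 × 30 | 0 | 2.45, 343, 80% | 60% | 17% |
| 36 × 63.3 | 0 | 4.12, 554, 94% | 76% | 21% |
| 36 × 63.3 | 0.5 | 4.91, 465, 90% | 68% | 18% |
| 36 × 63.3 | 0.8 | 6.14, 371, 83% | 57% | 14% |
| 36 × 63.3 | 1.0 | 7.28, 313, 76% | 49% | 12% |

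Example, CV 0.8 and ICC 0.05: (1 + 0.64) × 63.33 = 103.87; DE = 1 + 102.87 × 0.05 = 6.14; 2,280/6.14 = 371. CV 0 is a limiting case that 76 physicians in 36 clusters cannot reach. At ICC 0.05 the two structures break even at a CV of about 0.37.

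**5. Three-level check.** Assume correlation 0.05 between patients of one physician and 0.025 between patients of different physicians in one cluster. With k = 76/36 = 2.11 physicians per cluster, DE = 1 + 29 × 0.05 + 30 × ((1 + CV²)k − 1) × 0.025. At CV 0.8 this is 1 + 1.45 + 1.85 = 4.30, effective N 531, power about 94%. At CV 1.0 it is 4.87, effective N 468, power about 90%.

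**The case against.** The strongest reply is that the mismatch may cost nothing. The trial enrols nearly twice the calculated number of patients. With a small ICC and fairly even clusters, its power equals or exceeds that of 41 × 30, and under the three-level correlations assumed above it stays at 90% or more even at CV 1.0. The two-level formula also treats patients of different physicians as no less alike than patients of one physician, which the article's own model does not assume. All of this stands, and it rules out the claim that the trial is underpowered because of this mismatch.

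Three further inferences are tempting and are not supported:
- **Clusters of 30 to 300 patients.** A reader might take this from the honorarium tiers, which run from one or two physicians to ten or more. Those tiers are a payment scale for clinics. With 36 clusters in 22 clinics, a clinic's physician count need not be its cluster's count. No section gives physicians per cluster.
- **36 clusters as a shortfall from 41.** The article foresees recruitment difficulty, and 36 lies between its two scenarios. The fault is that both scenarios assume 30 patients per cluster, so neither covers the trial.
- **Table 5 as a contradiction of 1230.** An expected 1,500 to 2,400 forms exceeds a required 1230 and does not conflict with it as a minimum. Its value here is that it confirms the per-physician quota.

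It can also be said that the ICC of 0.6 and the 80/20 user split are larger faults. At ICC 0.6 with equal sizes, the change of structure moves power by only about two points (23% to 21%). That is fair, but correcting those inputs while keeping 30 per cluster would still describe the wrong design.

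The condensed form of an article is no answer, because the article prints the cluster number, cluster size, observations and power itself.

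**Conclusion.** The point holds as an internal contradiction. The cluster is a group practice, the power calculation gives it one physician's quota, and the trial described has 36 unequal clusters averaging 63.3 patients. This conclusion needs no assumption about ICC or cluster-size variation: the stated 90% and 80% are figures for other designs.

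The size and direction of the error are not established. At an assumed ICC of 0.05, power ranges from 94% down to 76% as CV goes from 0 to 1.0, against 92% for 41 × 30. At ICC 0.10 it is at best level with 41 × 30. At the stated 0.6 it is lower at every CV, but both structures are then far below 90%. A reader might infer a proven loss of power; the documents do not support that, since they give no distribution of physicians per cluster and their one ICC is incompatible with their stated power. The power statement should be corrected, and the correction has to name its ICCs.

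**What to change.** Recompute power, or the detectable intention-to-treat difference between the randomised arms, for 36 clusters, 76 physicians and 30 patients per physician. Use the actual number of physicians in each cluster, which must be known because randomisation is blocked on it. State and justify two correlations, within physician and within cluster across physicians, to match the three-level model already planned. Obtain the result by simulation or from a three-level design effect that allows for unequal cluster sizes, and show a range of plausible ICCs. Replace the 41-cluster and 28-cluster statements with these figures and align the powering claim in the Benefits section.

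The cost is a recalculation and a few sentences. No extra patients are needed. The stated power may become less favourable.

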Research has shown a majority of patients completing the FOBT do so within 4 to 6 weeks [20]. In order to allow adequate time to complete the FOBT and return it to the laboratory, patients will be given four months to do so. Those patients not returning their FOBT test within a period of four months will be scored as failing to complete the FOBT test.

Analysis of results will be based on the intention to treat (ITT) model. All Statistical analysis will be performed using SAS 9.2 ® software. Categorical variables will be compared using the Chi-square test. The time taken to return FOBT cards will be analyzed with Cox’ Proportional Hazards Regression analysis. Due to the clustered design, study outcomes will be measured at the level of the patient, family physician, and medical clinic/cluster. The analysis will utilize multi-level logistic regression that accounts for variance among patients with the same FP, FP within the same cluster, and among the clusters. The SAS® GLIMMIX procedure will be used to model patient FOBT completion rate (response variable). This will enable evaluation of the rate of patient FOBT compliance within medical clusters and individual FPs. Sources of variance included in the model will include cluster level (treatment, electronic medical record or paper charts, PIN and/or UPCON membership), family physician level (gender, solo/group practice), and patient level (age, gender, socioeconomic status, and previous FOBT screening history) variables as well as random variation.

A computerized randomization number list will be used to select 10 patients per FP to be contacted for a Post-Study Follow-Up Survey (Additional files 4 and 5) conducted by telephone. Only those patients providing permission to be contacted will be included. Those patients surveyed will be asked for permission to document their Personal Health Identification Number which will facilitate future studies conditional to Health Research Ethics Board (HREB) approval of analysis of repeat colorectal cancer screening behavior over time.

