### Benefits

There are a number of benefits of the study protocol which are outlined as follows:

(1) The pragmatic design and flexibility of the protocol for each medical practice ensured it reflected the “real world” clinical practice environment and its inherent variability. This approach will produce findings that are generalizable and relevant to community-based family practice and will increase translation and application of evidence-based findings into the clinical practice setting. The study was powered to detect an absolute increase in CRC screening rates of 15% by the intervention. This is a realistic and clinically significant improvement.

(2) The multi-disciplinary team working together on this project represent multiple stakeholder opinions and contributions (primary care providers, primary care researchers, policy makers, and patients). It also reflects a variety of providers/practitioners all of which enhance the pragmatic nature of the design and findings. Working collaboratively on this research project facilitated creation of new networking opportunities and partnerships that have the potential to support future primary healthcare research that inform evidence-based family practice.

(3) Findings will allow us to describe the degree of variability in screening rates among the medical clinics and practitioners involved in the study and, the rates of internet usage among the age category 50–74 for a health-related issue, and more specifically, CRC information and screening.

(4) Findings will provide valuable patient feedback about the FOBT and the common issues related to completion/non-compliance with the test.

(5) The study is highly representative of the community-based clinical practice environment and included a variety of FPs from a number of different areas in the city and practice settings.

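### The stated 90% and 80% power is for users versus non-users of the aids (20:80), not for the randomised intention-to-treat comparison, yet it is presented as power for the intervention

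*Protocol article*

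**What the plan says.** The section on sample size, randomization and statistical analysis bases its power on a logistic regression. Its 1230 observations are split so that "80% are in the group that does not utilize the supplied intervention/magnet and 20% are in the group that does utilize" it, and this number "will achieve 90% power at a 0.05 significance level to detect a change from the baseline value of 0.400 to 0.550", which "corresponds to an odds ratio of 1.833". A fallback follows: "a logistic regression with a cluster size of 28 (840 observations) achieves 80% power with the same outcomes".

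The same section says "Analysis of results will be based on the intention to treat (ITT) model" and enters treatment in the model as a cluster-level variable. The Abstract also labels the primary endpoint intention to treat, and the Primary outcome section defines it as the proportion completing the test in each group. Under Experimental treatment group, every intervention patient receives a magnet, and contact with the telephone line or website is left to the patient.

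The Benefits section then states: "The study was powered to detect an absolute increase in CRC screening rates of 15% by the intervention".

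**The concern.** Clusters are randomised to control or intervention, so the 20:80 split cannot be an allocation ratio. It is a forecast of what patients do after randomisation. The power calculation and the primary analysis therefore address different contrasts. Users choose themselves and may differ from non-users in their readiness to be screened. The arm comparison is protected by randomisation, but it averages users together with intervention patients who never open the aids.

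The article gives no power for the arm comparison, and the Benefits sentence invites the reader to carry the 90% over to it. The Discussion links possible changes in screening policy to the result. If the aids worked in users as assumed, the arm comparison could well be non-significant, and that result could be misread as adequately powered evidence against the aids.

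**Working it through.** **Inputs from the article.** Completion 0.40 and 0.55; 20% users; "a cluster size of 41 clusters each enrolling 30 to 35 patients" (41 × 30 = 1230); fallback 28 × 30 = 840; stated ICC 0.6. The Abstract gives 36 clusters and 76 physicians with 30 patients each, which is 2,280 patients, or 63.3 per cluster.

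**Assumptions that the article does not give.** Two-sided 0.05, 1:1 arms, equal clusters, ICC 0.02–0.05, and no effect of the magnet in patients who do not use the aids.

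**1. The plan's own figure.** The odds ratio is (0.55/0.45)/(0.40/0.60) = 1.833, as stated. For logistic regression on a binary covariate with prevalence B = 0.2 and overall rate P = 0.8 × 0.40 + 0.2 × 0.55 = 0.43:

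N = [z₁√(P(1−P)/B) + z₂√(p₀q₀ + p₁q₁(1−B)/B)]² / [(p₁−p₀)²(1−B)]

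- 90% power: (1.960 × 1.107 + 1.282 × 1.109)² / 0.018 ≈ 716.
- 80% power: (1.960 × 1.107 + 0.842 × 1.109)² / 0.018 ≈ 535.

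Without clustering, 1230 and 840 patients would give 98.9% and 93.9%. The stated pairs imply design effects of 1230/716 = 1.72 and 840/535 = 1.57, that is, ICCs of about 0.025 and 0.020 with 30 per cluster. Taken literally, an ICC of 0.6 gives a design effect of 1 + 29 × 0.6 = 18.4 and power of 17% and 13%. So the 90% and 80% do not follow from the stated inputs, but at 20:80 they are consistent with a small ICC.

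**2. Dilution.** Arm difference = share of the intervention arm using the aids × effect in users.

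- 20% of all patients are users, hence 40% of the intervention arm at 1:1: 0.40 × 15 = 6 points.
- 20% of the intervention arm are users: 0.20 × 15 = 3 points.

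Conversely, a 15-point arm difference would need users to gain 15/0.40 = 37.5 points, or 15/0.20 = 75 points (40% to 115%, impossible; the ceiling is 0.20 × 60 = 12 points).

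**3. Power of the arm comparison.** Power = Φ(d/SE − 1.96), with SE = √[(p₀q₀ + p₁q₁)·DE/n per arm] and DE = 1 + (m−1)·ICC. For example, with 1230 patients, 6 points and no clustering: SE = √[(0.24 + 0.2484)/615] = 0.0282; 0.06/0.0282 − 1.96 = 0.17; power 57%.

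| Patients | ICC (assumed) | DE | 3 points | 6 points | 15 points |
|---|---|---|---|---|---|
| 1230 | none | 1 | 19% | 57% | >99% |
| 1230 | 0.025 | 1.73 | 13% | 37% | 98% |
| 1230 | 0.05 | 2.45 | 10% | 27% | 93% |
| 840 | none | 1 | 14% | 42% | 99% |
| 840 | 0.025 | 1.73 | 10% | 27% | 92% |
| 840 | 0.05 | 2.45 | 8% | 20% | 80% |
| 2,280 (36 clusters) | 0.02 | 2.25 | 16% | 49% | >99% |
| 2,280 (36 clusters) | 0.05 | 4.12 | 11% | 30% | 95% |

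**4. Detectable arm difference.** Solving the same formula for 36 clusters and 2,280 patients at 80% power gives 8.7 points (ICC 0.02) to 11.8 points (ICC 0.05).

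**The case against.** A reader might infer that the trial is simply not powered for its primary analysis. The article does not support that. If the whole intervention arm really gained 15 points, the last column of the table shows power close to or above the stated figures at these ICCs, because equal arms are more efficient than a 20:80 split. Read literally as power to detect 15 points, the Benefits sentence could even be defended at a small ICC. What fails is the source of the figure, and the plausibility of 15 points between arms when the plan itself expects 20% use.

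The magnet might also act without use of the aids, for instance as a reminder; the Background lists forgetting among the reasons for non-completion (3%). Any such effect would make the dilution milder. The article states none and sizes the trial on use.

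What was actually run is uncertain. A 50:50 split with 0.6 entered as a covariate R-squared gives 91.7% and 78.9%, close to the stated values, so a misdescribed software input cannot be excluded. The text as published would still need correcting.

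Finally, the Primary outcome section also plans to compare patients who accessed the aids with controls. A calculation based on use has some bearing on that evaluation, but cannot stand in for power of the intention-to-treat comparison.

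**Conclusion.** The point holds in this form: the only power given is for a contrast formed after randomisation, and the Benefits section presents it as power for the intervention. Under the plan's own 20% use, and if the aids act only through use, the assumed 15-point gain in users leaves 6 or 3 points between arms. Neither stated sample size reaches 60% power for that, even with no clustering. With 2,280 patients, power for 6 points is at best 49% over the assumed ICC range, so a non-significant result would be about as likely as not in that case and more likely in the others.

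The mismatch of contrasts stands on the text alone. The size of the shortfall rests on the 1:1 arms, the assumed ICCs, the reading of the 20%, and no effect without use. The stated ICC of 0.6 is a separate problem and does not rescue the figure.

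**What to change.** In the sample size section, replace or supplement the user/non-user calculation with power for the arm-level intention-to-treat contrast. State the allocation ratio, the design effect with its ICC, the expected use and whether its denominator is all patients or the intervention arm, and the diluted difference that follows. Give the detectable arm difference: about 9–12 points at 80% power for 36 equal clusters and 2,280 patients, at an assumed ICC of 0.02–0.05.

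In the Benefits section, say that the calculation assumed 15 points between users and non-users of the aids. If a 15-point effect on the whole arm is meant, say so and explain how it fits with 20% use.

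The cost is a re-run of the calculation and some rewording. No extra patients are needed, but the power stated for the effect the plan itself implies will be lower.
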